**Methods and analysis:**

MODERNISED (ISRCTN17299125) is a multicentre prospective, non-interventional, case–control study. We aim to recruit 1000 adult participants with a recent cancer diagnosis, 250 adult participants with symptoms of cancer where a cancer diagnosis was ruled out by the National Health Service (NHS) standard of care and 100 healthy adult volunteers. Cancer tissue of origin (ToO) will include bladder, breast, colorectal, lung, melanoma, oesophageal, ovarian, pancreatic, prostate and renal. Participants in the two non-cancer cohorts who are later diagnosed with cancer will be moved to the cancer cases cohort. The primary aim is to train and validate a machine learning algorithm to detect cancer, which will be evaluated by AUROC. Secondary aims include training and validating an algorithm to predict ToO and stage of cancer, exploring differences in performance by demographics and estimating how sensitivity varies across specificity cut-offs of 95%, 99% and 99.9%. These results will provide a statistically powered estimate of how well the Enlighten test can discriminate between individuals with and without cancer, which can then be validated for clinical use in further research.

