### Model training and validation

Participants will be randomised in a 3:1 ratio with varying permuted blocks, balanced by cancer ToO and stage, into a model training (75% of participants) or model validation (25% of participants) set. The randomisation list will be pregenerated by a statistician at SCTU. Those in the model training set will have their cohort (cancer case, symptomatic control and asymptomatic control), age and sex shared with PD to train machine learning algorithms in combination with amino acid concentrations. PD will be blinded to the diagnostic status of participants in the model validation set.

Symptomatic controls and healthy volunteers may later be diagnosed with cancer (and therefore move into the cancer cases cohort). Randomisation will therefore only occur on three occasions during the study to reduce the impact of imbalance between building and validation sets. All participants and care providers will remain blinded. Participants will not be randomised more than once. The occasions are as follows: (1) when the amino acid concentrations have been measured for the first batch of 20 participants’ samples with complete data (to stress test processes). (2) When the T_1_ visit has occurred for 50% of the target participants in the breast, colorectal, prostate and lung cancer cohorts. (3) When the T_1_ visit has occurred for all participants, and all data have been returned.

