### Sample size calculation

A prediction model for a binary outcome (cancer yes/no status, prevalence 74%), 15 prediction parameters (five amino acids Cysteine, Reduced Cysteine, Lysine, Tryptophan and Tyrosine, potentially age and sex, and allowing for additional interactions in models), Nagelkerke’s r-squared of 20% and target shrinkage of 10% requires a minimum sample size of 916 (678 events) to reduce overfitting.^14^ Rounded up to 750 events and allowing a random 3:1 split between data available for model building and validation, the total required sample size is 1000 events, with 250 symptomatic controls, and 100 healthy volunteers, a total of 1350.

Of the 1350, the total sample size for validation would be 337, with 250 cancer cases, 62 symptomatic controls and 25 healthy volunteers. Because the distribution of the linear predictor derived from the prediction model is not known in advance, the anticipated Area Under the Receiver Operator Curve (AUROC) can be used to determine the required sample size for validation.^15^ Using this simulation approach with a target CI width of 0.1, the prediction model’s AUROC must be at least 0.84 to validate the model with sufficient accuracy with 337 individuals. As the pilot data demonstrated an AUROC of 0.98, it seems reasonable to assume an AUROC of 0.84 or higher can be achieved within this study.

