### Analysis plan

Baseline medical history, concomitant medications, demographics and Index of Multiple Deprivation will be summarised using descriptive statistics by cohort. The number of symptomatic controls and healthy volunteers who are later diagnosed with cancer and moved into the cancer cases cohort will be presented.

PD will train machine learning algorithms for diagnostic status, ToO and cancer stage. The output for diagnostic status will be a continuous risk score. The output for ToO will be one of the 10 cancers involved in the study, and may include the percentage chance for each ToO. The output for cancer stage will be either stage I, stage II, stage III or stage IV, and may include the percentage chance for each stage. Statisticians at SCTU will produce an AUROC plot in the model training and validation groups for diagnostic status. The apparent c-statistic will be calculated and adjusted for optimism using bootstrapping^16^ with accompanying 95% CIs. Sensitivity will be calculated in each group at cut-offs of 95%, 99% and 99.9% specificity with accompanying 95% CIs. Accuracy of the ToO and cancer stage predictions will be calculated in the model training and validation groups with accompanying 95% CIs.

These analyses will be repeated, stratified by early stage (stage I or II) and late stage (stage III or IV) cancer; ToO; symptomatic controls and healthy volunteers; age band at recruitment; biological sex at birth; availability of screening programme for cancer (screening test available (breast, cervical, colorectal and lung) or not available). All analyses will be conducted in R V.4.4.2 (or higher) or STATA V.17 (or higher).

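### The planned controls cannot support sensitivity at 99.9% specificity, and support 99% only very imprecisely

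*Protocol article*

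**What the plan says.** The abstract lists among the secondary aims "estimating how sensitivity varies across specificity cut-offs of 95%, 99% and 99.9"%. The Analysis plan section commits to it: "Sensitivity will be calculated in each group at cut-offs of 95%, 99% and 99.9% specificity with accompanying 95% CIs". The groups are those of the sentence shortly before: "Statisticians at SCTU will produce an AUROC plot in the model training and validation groups for diagnostic status". The same section then repeats the analyses by several strata, among them symptomatic controls and healthy volunteers separately.

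The Sample size calculation section gives the numbers available: "the total required sample size is 1000 events, with 250 symptomatic controls, and 100 healthy volunteers, a total of 1350". For the held-out part, "the total sample size for validation would be 337, with 250 cancer cases, 62 symptomatic controls and 25 healthy volunteers". That section sizes model building on shrinkage and validation on the width of the AUROC interval. It does not consider the three specificity targets.

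The article does not say in which data the cut-offs are set, whether they are carried from training to validation, or how the intervals for sensitivity are formed.

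**The concern.** Specificity is estimated from controls alone, and this design has few of them: about a quarter of participants overall and 87 in the validation set. A specificity of 99.9% means one false positive per 1,000 controls, so an empirical cut-off at that level needs a control sample of that order. With far fewer, the highest-scoring control sets the cut-off, and its true specificity is usually below the label on the row.

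Sensitivity is then read at a more lenient cut-off than stated, so it is overstated. The Discussion section envisages a rule-in tool, and for that use the high-specificity rows are the ones readers will look at first.

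**Working it through.** **Inputs.** Validation: 250 cases, 62 symptomatic controls and 25 healthy volunteers (Sample size calculation). All controls: 250 + 100 = 350; with the 3:1 split (Model training and validation) about 263 are in training. Targets: 95%, 99% and 99.9% (Analysis plan). AUROC values: 0.84, the minimum named for validation, and 0.98, the pilot value (Sample size calculation).

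**The plan's own figures reproduce.**
- Development: the maximum R-squared at 74% prevalence is 0.682, so the Cox-Snell value is 0.20 × 0.682 = 0.136. Then n = 15 / [(0.9 − 1) × ln(1 − 0.136/0.9)] = 916, and 0.74 × 916 = 678 events, as stated.
- Validation: with Newcombe's standard error, the AUROC interval at n = 337 is 0.098 wide at AUROC 0.84 and 0.1005 at 0.83, which agrees with the stated threshold of 0.84.

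**Step size.** 1/87 = 1.15 points. The attainable values next to the targets are 86/87 = 98.85% and 87/87 = 100%.

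**False positives allowed,** floor[m × (1 − specificity)]:

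| Controls m | 95% | 99% | 99.9% |
|---|---|---|---|
| 87 (validation) | 4 | 0 | 0 |
| 62 (symptomatic) | 3 | 0 | 0 |
| 25 (healthy) | 1 | 0 | 0 |
| 263 (training) | 13 | 2 | 0 |
| 350 (all) | 17 | 3 | 0 |

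In the validation set, and within either control type, the 99% and 99.9% rows share one cut-off and hence one sensitivity.

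**What zero false positives shows.** The exact two-sided 95% lower limit is 0.025^(1/m): 95.8% for 87, 94.2% for 62 and 86.3% for 25. The chance that the highest control score truly lies at 99.9% specificity or above is 1 − 0.999^m: 8% for 87 and 23% for 263.

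**Controls needed.** One expected false positive needs 100 controls at 99% and 1,000 at 99.9%. For zero false positives to give a one-sided 95% lower limit at the target, 0.99^m ≤ 0.05 needs 299 controls and 0.999^m ≤ 0.05 needs 2,995.

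**Size of the error (assumed equal-variance binormal scores).** The separation is d = √2 × Φ⁻¹(AUROC), which is 1.406 at 0.84 and 2.904 at 0.98. True sensitivity at specificity s is Φ(d − Φ⁻¹(s)). The reported figures come from simulating 250 cases, with the cut-off taken from the 87 controls.

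| AUROC | Row | True sensitivity | Mean reported | Middle 95% of estimates |
|---|---|---|---|---|
| 0.84 | 99% | 0.18 | 0.17 | 0.02 to 0.38 |
| 0.84 | 99.9% | 0.05 | 0.17 | as 99% row |
| 0.98 | 99% | 0.72 | 0.66 | 0.29 to 0.88 |
| 0.98 | 99.9% | 0.43 | 0.66 | as 99% row |

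**Intervals, if cut-offs come from the validation controls.** For sensitivity at the nominal specificity, a percentile bootstrap that re-derives the cut-off covers 94% to 95% in the 95% row, 70% to 74% in the 99% row and 12% to 16% in the 99.9% row (ranges over the two AUROC values).

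**The case against.** Much can be said for the plan, and most of it stands.

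- **Where cut-offs are set.** A reader might infer that the plan re-derives them inside each group. The wording suggests this, since sensitivity is calculated in each group, but does not state it. The full protocol or SAP, not shown, may fix it.
- **Intervals.** A reader might infer that all the intervals will be wrong. No interval method is named for sensitivity. A plain binomial interval around a cut-off chosen in the same controls would ignore the cut-off's own uncertainty, but in the 95% row a bootstrap deals with that.
- **The 99% row.** It is not beyond estimation. 86/87 is close to 99%, and taking the nearest attainable value would separate the two rows. At AUROC 0.84 even the zero-false-positive cut-off is nearly unbiased for it. The difficulty is precision.
- **What locking buys.** A reader who simulates might conclude that locking cut-offs in training lifts binomial coverage from 47% to 95%. Those figures concern different quantities: sensitivity at the nominal specificity and sensitivity at the cut-off actually used. Like for like at AUROC 0.84, locking on 263 controls gives about 70%, 55% and 35% for the nominal target in the three rows, against 47%, 34% and 15% with 87. For the realised cut-off, both approaches give about 95%.
- **Strata.** Controls have no stage or tissue of origin, so those repeats need not shrink the control set. The split by control type does.
- **Importance.** This is a secondary aim, and the article itself calls for further validation before clinical use.

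None of this rescues the 99.9% row. Its failure follows from the number of controls, which the article fixes, and no choice of interval or source of cut-off changes that.

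**Conclusion.** The point holds in this limited form. The 99.9% row cannot be estimated empirically with 87, 263 or all 350 controls. In the validation set it duplicates the 99% row under an at-least rule, and it carries a specificity that the data support only down to 95.8%. Its sensitivity would be overstated, by about 12 points at AUROC 0.84 and 23 points at 0.98. The 99% row is estimable but very imprecise.

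The counts, steps and exact limits rest on the article's numbers alone. The sensitivities, their spread and the coverage figures rest on the binormal assumption. The criticism of a plain binomial interval is conditional on cut-offs being taken from each group's own ROC curve. The primary AUROC analysis and its sample size are not affected.

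**What to change.** 1. Delete the 99.9% row, or relabel it as the cut-off with zero observed false positives and print the exact lower limit for specificity beside it.
2. State that the 95% and 99% cut-offs are set once, in the training controls, from cross-validated scores, and are applied unchanged to the validation set and to every stratum.
3. Report realised sensitivity and realised specificity side by side, each with an exact 95% interval, so that the interval refers to the cut-off actually used.

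The cost is a change of wording in the protocol and SAP, plus one deliverable that the article does not mention: the company that trains the algorithms would have to supply cross-validated scores for the training participants. The 99.9% row is lost, and realised specificity in validation may differ from the nominal 95% or 99%. No change to recruitment is needed.

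### The 99.9% specificity cut-off is finer than the control numbers can resolve: it allows zero false positives among the 87 validation controls, and among all 350

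*Protocol article*

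**What the plan says.** The Abstract (Methods and analysis) lists among the secondary aims "estimating how sensitivity varies across specificity cut-offs of 95%, 99% and 99.9" per cent. The Analysis plan carries this out: "Sensitivity will be calculated in each group at cut-offs of 95%, 99% and 99.9% specificity with accompanying 95% CIs". The groups are the training and validation sets, and the analyses are then repeated in strata that include control type. The score being cut is continuous: "The output for diagnostic status will be a continuous risk score".

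The Sample size calculation gives the validation set as 337 people, "with 250 cancer cases, 62 symptomatic controls and 25 healthy volunteers". It justifies that number only by the width of the AUROC confidence interval. The article does not say in which set a cut-off is fixed. Nor does it say whether the rule is at least the target specificity, the nearest attainable value, or interpolation.

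**The concern.** Specificity is estimated from controls alone, and three quarters of this study are cases. With 87 controls in validation, the empirical specificity scale moves in steps larger than the 0.9-point gap between 99% and 99.9%. A cut-off named 99.9% then has to sit at or near the single highest control score, whose true specificity is usually lower. The sensitivity printed beside that label would belong to a more lenient test. A binomial interval around the sensitivity would not reveal this, because the error lies in where the cut-off sits. The Discussion looks ahead to rule-in use, where performance at very high specificity is the figure readers would look for.

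**Working it through.** **Inputs** (Sample size calculation; Model training and validation). Total: 1000 cases, 250 symptomatic controls, 100 healthy volunteers. Split 3:1. Validation: "the total sample size for validation would be 337, with 250 cancer cases, 62 symptomatic controls and 25 healthy volunteers". Validation controls: 62 + 25 = 87. All controls: 250 + 100 = 350. Training controls: 350 − 87 = 263.

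**The plan's own figures reproduce.**
- Development: n = P / [(S − 1) ln(1 − R²/S)] with P = 15, S = 0.9 and Cox–Snell R² = 0.20 × 0.682 = 0.136. This gives 15 / (0.1 × 0.1638) = 916, and 916 × 0.74 = 678 events.
- Validation: the closed-form standard error of the c-statistic (Newcombe's variant of Hanley–McNeil), with n = 337 and prevalence 0.74, gives a 95% CI width of 0.0975 at AUROC 0.84 and 0.1003 at 0.83. So 0.84 is the first 0.01 step that meets the 0.1 target.

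Neither calculation addresses specificity cut-offs.

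**Step 1: false positives allowed.** For at least specificity s among n controls, the number is the integer part of n(1 − s).

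| Controls | n | One false positive costs | 95% | 99% | 99.9% |
|---|---|---|---|---|---|
| Validation, all | 87 | 1.15 points | 4 | 0 | 0 |
| Validation, symptomatic | 62 | 1.61 points | 3 | 0 | 0 |
| Validation, healthy | 25 | 4.00 points | 1 | 0 | 0 |
| Training, all | 263 | 0.38 points | 13 | 2 | 0 |
| Whole study | 350 | 0.29 points | 17 | 3 | 0 |

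Under this rule 100 controls are needed before 99% allows one false positive, and 1000 before 99.9% does.

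**Step 2: true specificity at the highest control score.** For n controls with a continuous score this follows Beta(n, 1). The mean is n/(n + 1), and the chance of reaching s is 1 − sⁿ.
- n = 87: mean 87/88 = 98.9%; chance of 99.9% or more is 1 − 0.999⁸⁷ = 8.3%; chance of 99% or more is 58%.
- n = 263: mean 99.6%; chance of 99.9% or more is 23%.
- n = 350: mean 99.7%; chance of 99.9% or more is 30%.

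**Step 3: what zero false positives shows.** The exact two-sided 95% lower limit is 0.025^(1/n): 95.8% for 0/87, 94.2% for 0/62, 86.3% for 0/25 and 99.0% for 0/350.

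**Step 4: effect on sensitivity.** The documents give no score distribution, so an equal-variance binormal curve is assumed. Separation is d = √2 × Φ⁻¹(AUROC), and true sensitivity at specificity s is 1 − Φ(Φ⁻¹(s) − d). Means at the estimated cut-offs come from 40,000 simulated studies.

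| AUROC | d | True sensitivity at 99.9% | Mean at highest of 87 controls | Ratio |
|---|---|---|---|---|
| 0.84 | 1.406 | 4.6% | about 17% | about 3.6 |
| 0.90 | 1.812 | 10% | 28% | about 2.8 |
| 0.98 | 2.904 | 43% | 66% | about 1.5 |

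At AUROC 0.84, with 250 cases, the observed value has a 95% range of 2% to 38%. The cut-off is too lenient in 0.999⁸⁷ = 92% of studies.

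**Step 5: other empirical rules, AUROC 0.84, true sensitivity 4.6% at 99.9%.**
- Nearest attainable, 87 controls: 99% becomes 1/87 (98.85% observed, mean true specificity 97.7%) and 99.9% becomes 0/87. The points differ, but the second is still the highest control score.
- Linear interpolation of quantiles, 87 controls: the 99.9% line has mean true specificity 98.8% and sensitivity 17.3%; the 99% line has mean true specificity 98.0%.
- Cut-offs from 263 training controls, ignoring overfitting: 9% at 99.9% under the at-least rule, 10% with interpolation.
- All 350 controls pooled: 8% and 9% respectively.

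**The case against.** The best defence is that the article fixes neither the cut-off rule nor the set in which the cut-off is derived, and an analysis plan that is not shown may do so. That part stands, and it limits what can be said.

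- A reader might infer that 99% and 99.9% are bound to be the same point. They coincide in validation only under the at-least rule applied to that group's own ROC curve. Nearest-attainable, interpolated or training-derived cut-offs differ.
- A reader might infer that the aim as a whole cannot be met. It can in part: 95% and 99% separate in validation (4 against 0 false positives), and all three separate in training (13, 2, 0).
- A reader might infer that the 99.9% figure is certain to be too high. It is too high on average. The simulated range at AUROC 0.84 (2% to 38%) includes the true 4.6%.
- The ratio of about 3.6 belongs to AUROC 0.84, which the plan uses as a minimum for precision and not as its expectation. At the pilot's 0.98 the ratio is about 1.5. Both rest on the binormal assumption.
- Nothing can be said about the number of controls by age or sex, since the documents give no such distribution. Nor do they say that cut-offs are re-derived within strata.

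It is also fair that AUROC is the primary measure, that these cut-offs are a secondary matter absent from the aims listed in the Introduction, and that the article says further validation must come before clinical use. These points lower the severity. They do not rescue the 99.9% level: an analysis plan can choose a rule but cannot add controls, and a parametric tail, which the article does not mention, would be extrapolation.

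**Conclusion.** The concern holds for the 99.9% cut-off. From the plan's own numbers, that level allows zero false positives in validation, in training and in the whole study. At the highest of 87 control scores the chance that true specificity reaches 99.9% is about 8%. These results need only the control counts and a continuous score.

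Every empirical rule tested gave a sensitivity above the true value on average; the size of that excess depends on the assumed curve. The coincidence of 99% and 99.9% in validation is conditional on the at-least rule, and the 95% cut-off is not affected. Because the estimate is secondary and the primary AUROC analysis is untouched, this should be fixed but is not critical.

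**What to change.** In the Abstract and the Analysis plan, delete the 99.9% cut-off. Keep 95% as the main quantitative cut-off. Report any higher cut-off, including 99%, with its attained specificity (x/n false positives) and exact interval. Label the extreme point as sensitivity at zero observed false positives (0/n), never as 99.9%; in validation that is 0/87, with specificity at least 95.8%. Do the same in the control-type strata (62 and 25) and in any other stratum where cut-offs are re-derived. State that very high specificity has to be tested in a later study.

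Recruitment, the assay, the split and the primary analysis do not change. The cost is a wording change to the plan of a study already recruiting, and a less ambitious secondary aim.

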### The Proteotype Diagnostics Enlighten test

Proteotype Diagnostics (PD) have developed an alternative approach to MCED testing. Instead of measuring material released from tumours (cfDNA or ctDNA), amino acid concentrations are measured in plasma in the Enlighten test, which are affected by the immune response. Immune responses are stronger during the early stages of cancer^12^ and therefore may be used to improve the detection of stage I and II cancers. Machine learning (an ensemble subspace discriminant classifier) was applied to classify tested samples to cancer or non-cancer in a retrospective observational study of 77 cancer patients (breast, colorectal, pancreatic and prostate) and 20 healthy volunteers. A sensitivity of 78% at 100% specificity was achieved using Enlighten, and concentrations were further differentiated in early-stage cases.^13^

Southampton Experimental Cancer Medicine Centre (ECMC) responded to an open call for partnerships with PD to develop a study further evaluating the Enlighten test. Southampton Clinical Trials Unit (SCTU) then developed a research proposal with PD and ECMC as partners, which is academically sponsored by University Hospital Southampton Trust and jointly funded by the National Institute for Health and Care Research and the Office for Life Sciences (ref NIHR207538).

The primary aim of this study is to train a machine learning classifier to use amino acid concentrations from the Enlighten test to detect cancer (bladder, breast, colorectal, lung, melanoma, oesophageal, ovarian, pancreatic, prostate and renal) in comparison to adult participants with symptoms of cancer where a cancer diagnosis was ruled out and healthy volunteers. Participants will be randomised, with 75% used to train the classifier and 25% used to validate the classifier. Secondary aims include:

Training and validating a classifier to distinguish cancer patients from adult participants with symptoms of cancer, where a cancer diagnosis was ruled out.Training and validating a classifier to distinguish cancer patients from healthy controls.Evaluating discrimination and sensitivity by tissue of origin (ToO), stage, age, sex at birth and availability of a UK cancer screening programme.Training and validating a classifier to predict ToO.Training and validating a classifier to predict cancer stage.

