### Machine learning training and validation

Machine learning techniques considered will include: random forests, support vector machines, ensemble subspace discriminant classifiers, XGBoost, neural networks and deep learning algorithms. The final modelling strategy will be informed by comparative predictive performance and computational cost. Triplicate values of the five amino acids (Cysteine, Reduced Cysteine, Lysine, Tryptophan and Tyrosine) will be used as input parameters (or combined as average readings), with potential additions of participant age and sex. Feature importance will be measured by Shapley values. Stratified cross-validation will be used to reduce overfitting.

One algorithm will predict diagnostic status (‘cancer’ or ‘no cancer’), a second will predict cancer ToO (bladder, breast, colorectal, lung, melanoma, oesophageal, ovarian, pancreatic, prostate and renal) and a third will predict cancer stage (I, II, III, IV). The trained algorithms will use amino acid concentrations (and potentially age and sex) to predict diagnostic status, ToO and cancer stage in the development and validation cohorts. These predictions will be provided to statisticians at SCTU to independently validate predictions against true status.

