## Discussion

This study will determine the diagnostic accuracy of machine learning techniques using the Enlighten test to detect cancer. This will be achieved by running the assay in a group of recently diagnosed cancer patients, patients who are symptomatic but cancer was ruled out, and participants with no symptoms or cancer diagnosis. Utility in guiding cancer diagnosis will also be assessed by determining the accuracy of the predicted ToO and stage of cancer. Cancer diagnosis will be collected and updated via local EHRs across five secondary care sites in the south of England. The potential applicability of the machine learning algorithms in future research will be assessed through a held-out dataset.

While this study focuses on 10 sites of cancer (bladder, breast, colorectal, lung, melanoma, oesophageal, ovarian, pancreatic, prostate and renal), additional ToO may be added, which will require model retraining in future research. This will reduce the risk of false results where a tested individual has a cancer that is not covered by the algorithm, which can delay the time to diagnosis. To improve the proportion of cancers detected early, a substantial number of cancer patients diagnosed at stage I or II must be recruited into the study. The research team have reviewed the throughput of recruitment sites in previous years, and recruitment will be monitored and potentially tailored to ensure that these requirements are met.

Theoretically, amino acids will improve the sensitivity for MCEDs to detect early-stage cancers in comparison to the more commonly used cfDNA and ctDNA techniques. If the Enlighten test does perform in this regard, then it could be used as a triage tool prior to expensive diagnostic imaging for individuals suspected of cancer. A reliable rule-in tool for cancer detection would reduce the overall demand for diagnostic imaging. This would, in turn, allow for individuals with a lower pretest probability of cancer to be tested, therefore increasing the rate of cancers detected early.

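### Sensitivity is read at a fixed specificity in each group, so on the natural reading the held-out set validates the score but no positive/negative rule, and specificity is never estimated

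*Protocol article*

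**What the plan says.** The Analysis plan describes the cancer/no cancer output in these words: "The output for diagnostic status will be a continuous risk score". It then states: "Sensitivity will be calculated in each group at cut-offs of 95%, 99% and 99.9% specificity", with 95% CIs attached. The groups are the model training and validation groups named just before that sentence. The CI method for sensitivity is not given.

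The abstract gives the primary aim as to "train and validate a machine learning algorithm to detect cancer, which will be evaluated by AUROC", and lists among the secondary aims "estimating how sensitivity varies across specificity cut-offs of 95%, 99% and 99.9" per cent. The secondary aims in the Introduction include "Evaluating discrimination and sensitivity by tissue of origin (ToO), stage, age, sex at birth". Specificity appears only as the fixed axis and is not listed as a result.

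On validation, the section Machine learning training and validation says: "These predictions will be provided to statisticians at SCTU to independently validate predictions against true status". The Discussion adds: "The potential applicability of the machine learning algorithms in future research will be assessed through a held-out dataset". The section Model training and validation keeps the model builder blind to diagnostic status in the validation set. No section carries a numeric cut-off from training to validation.

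**The concern.** A continuous score becomes a test only once a cut-off is attached. To have exactly 95% specificity in the validation group, the cut-off must be placed using that group's own control labels. A cut-off carried over from training would give some other specificity there, and that figure would need reporting. The plan lists no such figure.

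Three things follow if the sentence is applied as it naturally reads:

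- The held-out set shows how well the score ranks people, but not how a stated positive/negative rule performs.
- A fall in specificity between training and held-out controls would not appear in any listed output. The Discussion considers use as a triage or rule-in tool, for which specificity is the key property.
- The cut-off rests on a handful of control scores, and that uncertainty passes into the sensitivity estimate. A CI that treated the cut-off as known would be too narrow.

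**Working it through.** **Inputs.** From Sample size calculation: 337 people in validation, made up of 250 cases and 62 + 25 = 87 controls; 250 + 100 = 350 controls in all, hence 350 − 87 = 263 in training; design AUROC 0.84; pilot AUROC 0.98. Assumed here: equal-variance binormal scores.

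**The plan's own figure.** The plan says that AUROC must be at least 0.84 for a CI width of 0.1 with 337 people. A Newcombe-type standard error with prevalence 0.74 gives a width of 0.1003 at AUROC 0.83 and 0.0975 at 0.84, so the figure reproduces. The validation set was therefore sized for AUROC, not for sensitivity at a fixed specificity.

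**True sensitivity at 95% specificity.** The separation is √2 × Φ⁻¹(0.84) = 1.406. Sensitivity is 1 − Φ(1.645 − 1.406) = 0.406. The ROC slope at that point is 3.76.

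**Precision.** When the cut-off is estimated from controls, Var = Se(1−Se)/n_cases + slope² × Sp(1−Sp)/n_controls.

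- Case term: √(0.406 × 0.594/250) = 0.031.
- Control term, 87 validation controls: 3.76 × √(0.05 × 0.95/87) = 0.088.
- Control term, 263 training controls: 3.76 × √(0.05 × 0.95/263) = 0.051.

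| Quantity | Cut-off from | SD, formula | SD, simulation |
|---|---|---|---|
| Sensitivity at true 95% specificity | 87 validation controls | 0.093 | 0.090 |
| Sensitivity at true 95% specificity | 263 training controls | 0.059 | 0.059 |
| Sensitivity of the locked cut-off itself | fixed beforehand | 0.031 | 0.031 |

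The first two rows estimate the same quantity, and their ratio is 9.0/5.9 ≈ 1.5. The third row is a different quantity. Setting it against the first gives a ratio near 3 (about 2.3 at AUROC 0.98), but that is not a gain in precision for one target.

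**Coverage, if the CI ignored cut-off uncertainty.** In 20,000 simulated studies the cut-off was placed so that four of the 87 controls lay above it (the fifth-highest control score). An exact binomial 95% CI on the 250 cases covered the true sensitivity in about 51% of studies at AUROC 0.84, and in 52%, 51% and 64% at 0.78, 0.90 and 0.98.

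**True specificity of such a cut-off.** The true false-positive rate above the fifth highest of 87 control scores follows Beta(5, 83). Its central 95% range is 1.9% to 11.3%, so true specificity runs from about 89% to 98%, whatever the score distribution.

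**The higher cut-offs.** In 87 controls, 99% specificity allows 87 × 0.01 = 0.87 false positives and 99.9% allows 87 × 0.001 = 0.09. If the rule is to reach at least the target, both cut-offs become the highest control score. At AUROC 0.84 both then return a mean sensitivity of about 0.17, against true values of 0.179 and 0.046. Even 87/87 correct controls has an exact lower limit of 0.025^(1/87) = 95.8%.

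**The case against.** The article does not say outright where the validation cut-off comes from. That detail and the CI method may stand in the full protocol or SAP, which are not shown. This stands: the source of the cut-off is the natural reading, not a statement, and the 51% is conditional on an interval that the plan does not name. A bootstrap of cases and controls would carry the cut-off uncertainty, and the plan already bootstraps the c-statistic.

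The stated aim is to describe how sensitivity varies with specificity, which is a reading of the ROC curve, and validation for clinical use is left to later research. A reader might infer that nothing fixed is validated at all. The documents do not support that: a trained score is applied to held-out people whose labels are hidden from its builder, and is judged by AUROC.

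A reader might also infer that the planned sensitivity estimate carries three times the noise it needs. That compares two different quantities. For sensitivity at a true 95% specificity, the quantity the plan names, a training-derived cut-off also has sampling error.

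Finally, the split is random within the same sites and assay, so attained specificity should lie near its nominal value apart from sampling noise, and a shift in people outside the study would stay unseen. With 87 controls the check is also weak: if true specificity were 88%, an exact 95% CI would exclude 95% only about 61% of the time. This limits what the change can show, but it does not supply the missing specificity estimate.

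**Conclusion.** The point holds in limited form. As the Analysis plan naturally reads, validation specificity is set by construction, no held-out specificity is estimated, and no positive/negative rule is validated. The score itself is validated by AUROC. The resulting SD of about 9 points for sensitivity at 95% specificity depends on the binormal shape and on AUROC 0.84; at the pilot AUROC of 0.98 it is about 4.5 points. The 89% to 98% range for true specificity needs no distributional assumption. Undercoverage arises only if the interval treats the cut-off as known. Because clinical validation is deferred, this is a cheap and worthwhile improvement rather than a fault in the primary analysis.

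**What to change.** In the Analysis plan (or the SAP, if it is silent on this):

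1. Derive the numeric cut-offs from out-of-fold cross-validated scores of the roughly 263 training controls, and lodge them with the trials unit before validation predictions are scored.
2. Apply them unchanged to the validation set. Report sensitivity (n=250) and specificity (n=87) with exact 95% CIs, labelled as the performance of that fixed cut-off. The sensitivity SD is then about 3 points. As an example for specificity, 83/87 would be reported as 95.4% (88.6% to 98.7%).
3. Keep sensitivity at validation-derived specificity as a supporting ROC reading, with a CI that resamples both cases and controls.
4. State that 87 controls cannot confirm 99% or 99.9% specificity. Training does not resolve 99.9% either, since 263 × 0.001 = 0.26 expected false positives.

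The cost is some wording and a few numbers lodged in advance, with no extra participants or samples. The small downside is that attained validation specificity will not equal the nominal value exactly.
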